# Peer volunteers in an integrative pain management program for frail older adults with chronic pain: study protocol for a randomized controlled trial

**DOI:** 10.1186/1745-6215-15-205

**Published:** 2014-06-03

**Keywords:** protocol, peer volunteers, pain, non-pharmacological, physical activity, gerontology

## Abstract

**Background:**

Chronic pain is common among the older population. A literature review on pain management program showed that exercise, yoga, massage therapy, Tai Chi, and music therapy could significantly reduce pain. In spite of the proven benefits of pain management programs, these intervention programs were effective only in the short term, and older adults would resume their old habits. It has been suggested that interventions comprising some type of social support have great potential to increase the participation of older adults. Therefore, we propose the inclusion of peer volunteers in an integrated pain management program to relieve pain among frail older adults. This study aims to explore the effectiveness of an integrated pain management program supplemented with peer volunteers in improving pain intensity, functional mobility, physical activity, loneliness levels, happiness levels, and the use of non-pharmacological pain-relieving methods among frail older adults with chronic pain.

**Methods/Design:**

We intend to recruit 30 nursing home residents and 30 peer volunteers from the Institute of Active Ageing in Hong Kong in a group trial for an 8-week group-based integrated pain management program. There will be 16 sessions, with two 1-hour sessions each week.

The primary outcome will be pain levels, while secondary outcomes will be assessed according to functional mobility, physical activity, loneliness levels, happiness levels, the use of non-pharmacological pain-relieving methods, and through a questionnaire for volunteers.

**Discussion:**

In view of the high prevalence of chronic pain among older adults and its adverse impacts, it is important to provide older adults with tools to control their pain. We propose the use of peer volunteers to enhance the effects of an integrated pain management program. It is expected that pain can be reduced and improvements can be achieved among older adults in the areas of physical activity, functional mobility, loneliness levels, happiness levels, and the use of non-pharmacological pain relieving methods. Using these results, we will assess the need to conduct a larger study with a randomized controlled design.

**Trial registration:**

This trial was registered on 24 February 2014 at the Australian New Zealand Clinical Trials Registry (ANZCTR) with the trial number: ACTRN12614000195651

## Background

An aging population is a global phenomenon. As people get older, they become more vulnerable to age-related diseases and the resulting pain. The prevalence of chronic pain among community-dwelling older adults is high. For instance, in Hong Kong, 37 to 50% of community-dwelling older people suffer from pain [1,2]. The prevalence of pain among nursing home residents in Hong Kong may even be as high as 70% [3].

Chronic pain can have severe adverse impacts on older adults. The consequences of unrelieved chronic pain include hindered activities of daily living, depression and anxiety, decreased social interaction, impaired mobility, falls, sleep disturbance, malnutrition, and increased health care utilization and expenses [4]. These adverse effects of chronic pain may worsen pre-existing health problems, thereby increasing the burden on health care and social services.

Analgesics remain the primary method of managing chronic pain [4]. However, some older people prefer not to use pain medication and often request them only when the pain reaches an intolerable level. In a local study, 173 community-dwelling older persons were interviewed and only 47% of the participants used oral analgesic drugs to relieve their pain [5].

Due to the limited acceptance of pharmacological approaches to managing pain, an increasing number of studies are being conducted to examine the effectiveness of non-pharmacological strategies to relieve pain. In a literature review, Reid *et al.*[6] investigated the evidence on self-managed interventions for pain among older adults. A total of 27 articles were identified, including those that evaluated programs sponsored by the Arthritis Foundation and other programs such as yoga, massage therapy, Tai Chi, and music therapy. Among the reviewed studies, 96% showed positive outcomes, with a median reduction in pain scores of 23%.

Another 8-week integrated pain management program (IPMP) was carried out among Hong Kong nursing home residents [7]. A total of 535 older adults were randomized into an experimental group (n = 296) and a control group (n = 239). The participants in the control group only received regular care but not the IPMP. The participants in the experimental group received the IPMP, which included a 30-minute physical exercise program (PEP) and 30 minutes of either multisensory stimulation therapy or an arts and crafts activity each week. The PEP included exercises in muscle strengthening, stretching, and balancing, and was conducted in small groups of 10 to 15 older residents. In the multisensory session, relaxation techniques to control pain and the use of the five primary senses were taught. In the arts and crafts session, older adults made artwork such as photo albums, paper flowers, and paper fans to exercise their fine motor activities and for multisensory stimulation. Upon completing the program, the participants in the experimental group showed a significantly higher reduction in pain scores, higher happiness and life satisfaction scores, and lower scores in loneliness and depression than were observed among the control group; no significant differences were seen in the control group. A significant increase in the use of non-pharmacological methods of pain relief was also seen among the participants in the experimental group as compared to the control group.

Although the pain management program, which includes physical activity, has been shown to have health benefits and improve pain management among older adults [8], studies have found educational interventions to be effective among older adults only over the short term [9]. People who participated in these interventional programs often fell back into their old habits of inactivity after completing the program [10]. Therefore, it is important to develop interventions that can be sustained over time.

It is suggested that interventions with some type of social support, such as a ‘buddy’ system, have great potential to increase the participation of older adults in exercise and overall fitness activities [11], and will lead to greater adherence to such activities, as well as result in a higher level of enjoyment of them [12]. Social support interventions in community settings focus on changing physical activity behavior through building, strengthening, and maintaining social networks that provide supportive relationships for behavioral change. In general, these interventions involve making a ‘contract’ with companions to achieve specified levels of physical activity, or setting up walking or other groups to provide companionship and support while being physically active [11]. In a study conducted in the United States, 81 sedentary adults were randomly assigned to two 16-week group-based programs: 1) peer-delivered or 2) a ‘standard’ community-based exercise promotion intervention. No significant difference in moderate-to-vigorous physical activity (MVPA) minutes/week at week 16 was found between the two groups, but both reported significantly more MVPA minutes/week relative to baseline at week 16. Moreover, peer volunteers (PVs) enhanced the long-term maintenance of physical activity, as the active intervention group was able to maintain and slightly increase their PA behavior by the 18-month follow-up session, while the standard community intervention group began to return to their baseline levels. There was significantly more physical activity among the group with peer support relative to the standard community intervention group after 18 months [13].

The effectiveness of PVs was also studied in a fall prevention program. After a 10-week intervention program, participants (n = 52, aged 65 to 94) in the peer-led group reported a 27% decrease in falls and more weekly walking for 34 minutes compared with the control group (n = 25), who had been taught by a trained instructor and had been without peer support [14].

Our research team conducted a search of databases (PubMed and ScienceDirect) to study the application of PVs in intervention programs for older adults in Hong Kong from 1998 to the present. Four studies were identified, and they have been shown to achieve positive outcomes. However, the programs studied were those for healthy living, coping with stress, post-discharge support, and physical activity [15-18]. No pain management programs involving PVs were found. PVs were chosen over other forms of social support as the Hong Kong population is aging and people are living longer. After retirement, some older adults are still enthusiastic about serving the community. Therefore, we will select the PVs from the Institute of Active Ageing (IAA), which is dedicated to promoting active aging and the view of older adults as important contributors to society. As the IPMP has already been validated and published, and its effectiveness has been established, the effectiveness of the IPMP among older adults is well understood; however, whether this effect will be extended with the use of PVs is unknown. Therefore, in the present study we will attempt to test only the effectiveness of an IPMP that will be sustained by PVs.

The aim of this study is to determine the feasibility of PVs in an IPMP for Hong Kong older adults with chronic pain. According to the literature, pain management programs range from 4 weeks to 8 weeks. As the previous 8-week IPMP has already been validated, in this study we would also like to examine the dose-response relationship of an IPMP with PVs (that is, the possibly nonlinear association between intervention duration and pain intensity score). Our objective is to run a pilot study for a future main study with a randomized controlled design. It is hypothesized that the implementation of an IPMP supplemented with PVs for older adults with chronic pain will lead to improvements in levels of pain intensity, functional mobility, physical activity, loneliness, and happiness, and in the use of non-pharmacological pain-relieving methods.

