### Outcome assessment

#### Primary outcome

The primary outcome measure is pain intensity, which will be assessed using an 11-point numeric rating scale (NRS). The NRS is a line marked in equal segments from 0 (no pain) to 10 (worst possible pain). The NRS has been shown to be a reliable and valid measure of pain intensity and pain distress in older patients with persistent pain [23].

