#### Data analysis

The IBM-SPBB version 20 will be used to perform a statistical analysis. Descriptive statistics (frequency, %), mean (standard deviation)) will be used to describe the demographic data of the participants.

To determine the dose-response relationship of this intervention program on pain, a generalized estimating equation with quadratic and higher order terms will be used. To examine the intervention effect, a t-test will be used to compare the mean pain intensity, functional mobility, physical activity, loneliness and happiness levels, and use of non-pharmacological methods collected at four time points, that is, between P0 and P1, P1 and P2, P1 and P3 (for pain only), and between P0 and P2, P0 and P3, and P2 and P3 (for other variables). The Kolmogorov-Smirnov normality test will be used to examine the normality of the outcome variables. If the data do not follow a normal distribution, we will use the Wilcoxon Signed-rank test and the Mann-Whitney U test for within-group and between-group comparisons, respectively. A *P* value of <0.05 will be considered statistically significant. An intention-to-treat analysis will be conducted for any missing data. All data from the ‘I can do it’ booklet will be gathered and used to calculate the participation rate.

The questionnaires for the volunteers will be compared using the McNemar test and a pair sample t-test for quantitative data. Qualitative data will be analyzed using content analysis [31]. Sentences or parts of sentences will be identified as meaningful units in each questionnaire. The meaningful units will be categorized into themes related to the perception of program. The themes will be compared and discussed to establish the credibility of the interpretations.

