## Discussion

The 8-week group-based IPMP has already been validated and published, and its effectiveness has been established. Interventions that include some type of social support have great potential to increase participation and adherence, raising the question of whether the effects of an IPMP can be extended with the use of PVs. This study is aimed at evaluating the feasibility of using PVs in an IPMP for Hong Kong older adults with chronic pain.

This pilot study helps older adults to control their pain by providing a PV to encourage and accompany them. The limitations of this study should be noted. As it is only a pilot study lasting 12 weeks, long-term changes in the outcome measures cannot be evaluated. Moreover, there may be a ‘learning effect’, which will familiarize the participants with measuring instrument in the study as there will be a repeated measure of pain intensity in the beginning of all 16 training sessions. This study provides evidence for future, larger studies that utilize a randomized controlled design and a possibly longer follow-up time to adjust this ‘learning effect’ and to investigate whether PVs should be integrated in programs for older adults with chronic pain. This will help to promote health among older adults in the long term.

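### The declared aim is feasibility of peer volunteers, also stated as effectiveness, but the primary outcome is an uncontrolled before-after pain comparison that cannot answer it, and no feasibility measure is primary

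*Protocol article*

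**What the plan says.** The protocol article states its aim in two ways.

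- **Feasibility.** Background: "The aim of this study is to determine the feasibility of PVs in an IPMP for Hong Kong older adults with chronic pain". Discussion: "This study is aimed at evaluating the feasibility of using PVs in an IPMP for Hong Kong older adults with chronic pain".
- **Effectiveness.** Abstract, Background: "This study aims to explore the effectiveness of an integrated pain management program supplemented with peer volunteers in improving pain intensity", followed by five further participant outcomes. Main Background, shortly before the feasibility sentence: "in the present study we will attempt to test only the effectiveness of an IPMP that will be sustained by PVs".

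Under Primary outcome: "The primary outcome measure is pain intensity", on an 11-point numeric rating scale. The Design section describes a single group. Data analysis specifies t-tests between time points for pain and the five other participant outcomes, with significance at P<0.05.

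Data that bear on feasibility are collected. Each resident's booklet is stamped at every session attended. Data analysis says that booklet data will be "gathered and used to calculate the participation rate". The volunteers' questionnaire is a listed secondary outcome. It covers self-efficacy, satisfaction, delivery skills, barriers and facilitators, and is analysed by McNemar and paired t-tests and by content analysis.

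On the next step, the abstract's Discussion says: "Using these results, we will assess the need to conduct a larger study with a randomized controlled design".

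**The concern.** A pilot's primary outcome should answer the pilot's question. If the question is whether volunteers can be recruited, kept and relied on to run sessions alone, a pain score does not answer it. If the question is whether volunteers improve pain, a single group that receives programme and volunteers together cannot separate the two.

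What is at stake is how the pilot will be read. A significant fall in pain could be reported as support for volunteers when the programme alone would have produced it. A non-significant result in 30 residents could be read as failure although delivery went well. In either case the facts most needed for planning the randomized study, namely whether volunteers stay and deliver, would have no prominent place in the results.

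**Working it through.** **1. Aim against primary outcome.** Feasibility is declared twice (Background, Discussion) and effectiveness twice (abstract, Background). The primary outcome matches only the effectiveness version. The document does not say which aim governs.

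**2. Can the primary outcome speak to volunteers, on the article's own premises?** The Background describes a randomized study of the programme without volunteers in Hong Kong nursing homes (296 + 239 = 535 residents). Pain fell significantly more with the programme than with usual care. The Background then treats the programme's effectiveness as settled. Pain is therefore expected to fall here even if volunteers add nothing. The Background also cites a randomized peer-support study in which both arms had raised their activity by week 16 with no significant difference between them. The advantage of peers appeared at 18 months. The present follow-up ends at week 12.

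**3. Size of the problem (illustration).** Assumptions not in the documents: pain SD 2; within-person correlation r of 0.5 or 0.7; two-sided paired t-test at 0.05; n = 30; a mean fall δ unrelated to volunteers.

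- SD of change = 2·√(2(1−r)): 2.00 for r = 0.5, and 1.55 for r = 0.7.
- Standardized change d = δ / SD of change. The test statistic is noncentral t with 29 df and noncentrality d·√30.

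| δ (points) | P(P<0.05), r = 0.5 | P(P<0.05), r = 0.7 |
|---|---|---|
| 0.5 | 0.26 | 0.40 |
| 1.0 | 0.75 | 0.93 |
| 1.5 | 0.98 | >0.99 |

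A significant result on a pain contrast is thus quite likely with no contribution from volunteers. In the other direction, power at n = 30 is only 0.36 for d = 0.3 and 0.56 for d = 0.4, so a null result is also weak evidence. The article gives no effect size, SD or power for its 30 participants, so there is no sample-size figure to reproduce.

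**4. What delivery depends on, and what is measured.** Counts from the article:

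- 30 residents in groups of 15 make 2 groups. With one volunteer-only session a week for 8 weeks, that is 2 × 8 = 16 volunteer-only group sessions. The team observes these in the first two weeks only (2 × 2 = 4), which leaves 12.
- Weekly visits in weeks 9 to 12: 30 pairs × 4 = 120 visits, assigned to volunteers.
- Each resident keeps the same volunteer throughout, so losing a volunteer breaks a pair.

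Stamps capture resident attendance and show indirectly whether a session took place. They are not described as recording which volunteer was present, and nothing described logs whether a follow-up visit was made.

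**5. Can 30 support feasibility outcomes?** Exact (Clopper-Pearson) 95% limits: lower = Beta quantile 0.025 with (x, 31−x); upper = Beta quantile 0.975 with (x+1, 30−x). The counts are illustrative.

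| x of 30 | Proportion | 95% CI |
|---|---|---|
| 18 | 60% | 41–77% |
| 21 | 70% | 51–85% |
| 24 | 80% | 61–92% |
| 27 | 90% | 73–98% |

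These intervals are wide, but they separate poor from good uptake.

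**The case against.** The strongest reply is that feasibility is not ignored. The volunteer questionnaire is a listed secondary outcome, is administered four times, and asks directly about implementing and delivering the programme. A participation rate will be calculated. A pilot may also reasonably report clinical change, and a condensed article may leave numeric progression thresholds to a fuller document. All of this stands, and missing thresholds alone would be no finding. It does not remove the mismatch between the declared aim and the primary outcome, or the two competing aims, both of which are in the text.

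Several stronger readings are tempting but not supported:

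- *That every significance test concerns pain.* Five other participant outcomes and the volunteer questionnaire are tested too.
- *That no feasibility measure is among the outcomes.* The questionnaire is one; it is simply not primary.
- *That the decision on the larger trial rests on a p-value.* The abstract gives no rule. The preceding sentence lists expected improvements in residents, but the results referred to could include participation and the questionnaire.
- *That regression to the mean will produce the fall.* Entry requires pain or discomfort for more than three months, with no minimum score, so selection on a high pain score is not shown.
- *That imprecision in the SD of pain change at n = 30 makes the p-value worthless.* That imprecision concerns sizing a later trial. It does not settle what the p-value adds here.

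The authors could instead declare effectiveness the single aim. That would restore consistency, but a single group still could not isolate the volunteers' contribution.

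**Conclusion.** The point holds as a mismatch between objective and primary outcome, made worse by two competing statements of the aim. The decisive argument needs no outside figure: the article calls the programme effective without volunteers and has no comparison group, so a before-after fall in pain cannot be assigned to volunteers and says nothing about whether they can deliver. The probabilities of 0.26 to above 0.99 only illustrate this. They rest on the assumed SD, correlation and size of fall, and the conclusion does not depend on them. The matter is worth correcting, but it does not invalidate the pilot: the main feasibility data source exists, and 30 residents and 30 volunteers give usable, if wide, intervals.

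**What to change.** 1. State one aim, feasibility of peer volunteers, in the abstract, the Background (including the sentence that speaks of testing only effectiveness) and the Discussion.
2. Make these the primary feasibility outcomes: resident attendance from booklet stamps; volunteer retention with the same resident; and volunteer-only sessions and weekly visits delivered out of those scheduled. Define attendance over the 16 sessions before analysis. Report proportions with 95% confidence intervals, using the resident or volunteer as the unit where possible, because the group sessions are clustered. Read them alongside the volunteer questionnaire.
3. Keep pain as the lead clinical outcome, reported as mean change and SD with a 95% confidence interval. Say that its before-after p-value is not evidence for volunteers and not the basis for the larger trial mentioned in the abstract.

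The cost is small: a simple volunteer log of sessions and visits, some relabelling of outcomes, and the loss of the pain p-value's headline role. The article describes recruitment as still under way. The change should be dated and made before outcome data are examined.

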## Method/Design

### Design

It will be a single group trial.

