#### Evidence-based practice: Integrated pain management program (IPMP)

The participants will be given an 8-week group-based IPMP supplemented with PVs. Table 1 shows the details of the IPMP. We will follow the study design of a previous study [7]. There will be 16 sessions, with two 1-hour sessions each week.

**Table 1 T1:** Integrated pain management program (IPMP)

**Week**	**Session 1**			**Session 2**		
	**(research assistant and peer volunteers)**			**(peer volunteers only)**		
	Interactive teaching and sharing	Exercise	Entry	Revision	Exercise	Entry
		(20 minutes)	(10 minutes)	(30 minutes)	(20 minutes)	(10 minutes)
	(30 minutes)					
1	Introduction on pain	Deep breathing	Research assistant and PVs will work together with the participants to make entries in the ‘I can do it’ booklet on the activity of the day.	PVs will use the ‘I can do it’ booklet to review the content taught in the previous session and continue any remaining arts and crafts activities.	Deep breathing	PVs will work together with the participants to make entries into the ‘I can do it’ booklet on the activity of the day.
	Impact of pain					
	Drug therapy					
2	Hot pad and cold pad	Relaxation exercise			Relaxation exercise	
3	Music therapy	Warm-up exercise			Warm-up exercise	
4	Massage	Shoulder and neck exercise			Shoulder and neck exercise	
5	Use of five sensations as nondrug therapies: making a photo album	Lower arm exercise			Lower arm exercise	
6	Use of five sensations as nondrug therapies: making a bag of dried flowers	Towel dancing			Towel dancing	
7	Use of five sensations as nondrug therapies: tasting of tea	Towel dancing			Towel dancing	
8	Wrapped up	Whole body exercise			Whole body exercise	

Session 1 of each week aims to empower the older adults with knowledge of how to manage pain and to demonstrate the procedure of the selected exercise. The research assistant (RA) will lead the sessions and the PVs will help the RA to guide the participants in doing exercises and assist them in carrying out the activities. Session 1 includes:

1. 30 minutes of interactive teaching and sharing. The contents include an introduction on pain, the impact of pain, drug therapy, five sensation therapy (touch, smell, taste, hearing, and vision), making a photo album and bags of dried flowers, and a tea tasting.

2. 20 minutes of exercise. Specific exercises for the shoulder, neck, arms, and the whole body, and balancing and towel dancing will be taught.

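### The title announces a randomized controlled trial, but the design is one uncontrolled group, which supports only within-person change under the whole programme-plus-volunteer package

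*Protocol article*

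**What the plan says.** - **Title:** the paper is a "study protocol for a randomized controlled trial".
- **Design:** "It will be a single group trial". Samples and Setting describe 30 residents of one nursing home, all of whom receive the IPMP with PVs. No comparator or allocation is described.
- **Abstract (Discussion), end of Background, Discussion:** a randomized design is mentioned only for a later, larger study.
- **Background, rationale:** the IPMP effect is taken as established, but "whether this effect will be extended with the use of PVs is unknown". The next sentence reads "Therefore, in the present study we will attempt to test only the effectiveness of an IPMP that will be sustained by PVs". The stated aim is the feasibility of PVs in an IPMP, and the hypothesis is that the IPMP supplemented with PVs leads to improvements.
- **Data analysis:** t-tests between time points are offered as the way to examine the intervention effect. If normality fails, the Wilcoxon signed-rank test is named for within-group comparisons and the Mann-Whitney U test for between-group ones.
- **Background, earlier IPMP trial:** participants were randomized to regular care or to an IPMP consisting of a "30-minute physical exercise program (PEP) and 30 minutes of either multisensory stimulation therapy or an arts and crafts activity each week".
- **Evidence-based practice section:** the present study is said to follow the design of that earlier study, and then "There will be 16 sessions, with two 1-hour sessions each week".
- **Discussion, limitations:** short duration and a learning effect from repeated pain ratings are named. The lack of a control group and regression to the mean are not.

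**The concern.** Title and methods give two incompatible designs, and the analysis section contains a test that fits neither the single group nor any comparison the paper sets up. A reader who selects studies by title would take this one for randomized evidence.

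The second issue is what a fall in pain could be taken to mean. The rationale moves from the open question of whether PVs extend the IPMP effect straight to this study, and the analysis calls a before-after contrast the intervention effect. Together they invite the conclusion that PVs, or at least the programme, caused any change observed. Without a concurrent group that received the IPMP alone or usual care, neither conclusion can be drawn.

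A reader might try to fill the gap by setting the results beside the earlier IPMP trial. The weekly contact time differs, so that comparison would not isolate the PVs either.

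**Working it through.** **1. Design statements side by side.** The title says randomized and controlled; Design says one group. Every other mention of randomization refers either to a cited study or to a future one. The contradiction lies within the current text and does not depend on anything a fuller protocol might add.

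**2. Is there any pair of groups for the Mann-Whitney test?** Procedure says each session takes a group of 15, so 30 / 15 = 2 session groups. Both receive the same programme, so a contrast between them says nothing about the intervention. The volunteer questionnaires have their own tests (McNemar and paired t). For participant outcomes the between-group test therefore has no object.

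**3. What the within-group change contains.** For a mean change from P0 to P2 or P3 in one group:

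observed change = IPMP + PVs + added contact + time trend + regression to the mean + effect of repeated measurement

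There is one equation and there are several unknowns, so no term can be separated. The repeated-measurement term is admitted in the Discussion. The regression term cannot be sized. Eligibility requires pain for more than three months but sets no minimum score on the numeric rating scale, and the documents give no standard deviation, no correlation between repeated ratings and no indication that residents enrol when their pain is above its usual level.

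**4. Contact time.** Programme size as stated: 8 weeks x 2 sessions = 16 sessions, which reproduces.

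| | Earlier IPMP (Background) | This study (Table 1) | Ratio |
|---|---|---|---|
| Exercise, min/week | 30 | 2 x 20 = 40 | 1.33 |
| Teaching, revision, multisensory or arts, min/week | 30 | 2 x 30 = 60 | 2.0 |
| Booklet, min/week | 0 | 2 x 10 = 20 | – |
| Total, min/week | 60 | 120 | 2.0 |
| Total over 8 weeks | 480 min (8 h) | 960 min (16 h) | 2.0 |

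Four weekly PV visits in weeks 9 to 12 come on top. The 60-minute figure assumes that the weekly frequency in the description of the earlier trial applies to both 30-minute parts, which is the natural reading.

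**5. Would randomizing the same 30 residents solve it?** As an illustration, take 15 against 15, two-sided alpha 0.05, 80% power, normal approximation. The detectable standardised difference is (1.960 + 0.842) x sqrt(2/15) = 1.02. At assumed standardised effects of 0.3, 0.5 and 0.8 the power is 0.13, 0.28 and 0.59. A split of this sample would give a rough estimate of a PV effect, not a useful test.

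**The case against.** The strongest reply is that the paper is open about being a pilot. Its stated aim is feasibility, repeated in the Discussion. Its hypothesis concerns the IPMP supplemented with PVs, and the sentence quoted from the Background refers to the programme as sustained by PVs, not to PVs alone. The Discussion leaves to larger randomized studies whether PVs should be integrated, and it names the learning effect. A single-group pilot before a randomized trial is a legitimate choice, and anyone who reaches the Design section is corrected on the title.

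Most of this stands. A reader might infer that the authors claim to isolate the PV effect; the documents do not support that. A reader might also infer that regression to the mean is likely to produce a significant result by itself, with some calculable probability. The documents do not support that either, because the quantities needed are absent and there is no pain-score threshold at entry.

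On contact time, the documents propose no formal comparison with the earlier trial, and the second weekly hour is the PV-led session, so it is partly how the PV component is delivered. That too is fair. Peer support and extra contact remain inseparable, but this is a secondary point.

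The reply does not remove the false design label in the title, the between-group test, the causal wording in the rationale and analysis, or the absence of the missing control group and of regression to the mean from the limitations.

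**Conclusion.** The concern holds as a fault of labelling and interpretation, not as a case against running a single-group pilot. The title is wrong for the design described, and one named test has no groups to compare. The study can support feasibility findings and within-person change under the combined package. It cannot support an effect of PVs, or a causal effect of the package.

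The conclusion follows from the text and needs no numerical assumption. The one firm figure is the contact ratio of 2.0 (120 against 60 minutes per week), which rests on the reading of weekly frequency noted above. Even with equal contact, one uncontrolled group could not show a PV effect. Regression to the mean is a possibility of unknown size.

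**What to change.** - **Title:** call the study a single-group (uncontrolled) pilot study.
- **Background and Data analysis:** restate the hypothesis and the term intervention effect as within-person change from baseline under IPMP plus PVs, and say that no effect will be attributed to the PVs.
- **Data analysis:** delete the between-group Mann-Whitney U test for participant outcomes.
- **Discussion:** add the lack of a control group and regression to the mean to the limitations, beside the learning effect already named.
- **Evidence-based practice section:** reconcile the statement that the earlier study's design is followed with the different design and the doubled weekly contact, and note that the second hour is PV-led.

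The cost is wording, plus a check that the registry entry, which was not available here, describes the same design. No new data and no change to the conduct of the study are needed. If a PV effect is the real question, it belongs in the planned larger trial, with a concurrent group receiving the IPMP without PVs and with matched contact time.
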